#### Implementation outcomes

The RE-AIM framework was used to define implementation outcomes for evaluation (Table 3) [19, 20]. The following additional data collection activities will take place to measure these outcomes:Coverage and coverage equity. Treatment coverage will be assessed in several ways. CHWs will record key information about each MDA on paper data collection forms, including the number of treated children, adverse events experienced, and the number of days required for the distribution. Administrative coverage will be estimated using current estimates of the under-5 population from CSIs as the denominator and the number of children treated in each MDA according to the CHW data collection form as the numerator. Administrative coverage will be used for official reporting for all CSIs. Census coverage will be calculated using estimated eligible population denominators available from the pregnancy histories conducted in the monitoring CSIS. Administrative and census coverage will be compared to determine the validity of the administrative coverage estimates.Coverage evaluation surveys will be conducted in a randomly selected subset of CSIs to validate coverage estimates using caregiver self-report, to identify subgroups with low coverage to evaluate coverage equity, to understand reasons for low coverage, and to compare outcomes of different implementation strategies. Survey instruments will be developed based on standardized questionnaires used for neglected tropical disease program monitoring according to WHO guidance [21], and implementation strategies will be assessed using versions of the Acceptability of Intervention Measure, Intervention Appropriateness Measure, and Feasibility of Intervention Measures that have been modified to ensure cultural appropriateness [16]. Trained data collectors fluent in local languages will visit every household in selected CSIs and conduct the survey among caregivers of children eligible for the program after obtaining verbal informed consent. Surveys will take place within 1 week of the most recent MDA.In-depth interviews will be conducted after 2 and 4 years in a random sample of caregivers stratified by participation in the program as well as a random sample of CHWs and CSI leaders to identify barriers and facilitators to participation and implementation along with implementation strategies to improve uptake. Interview guides will be developed using the Consolidated Framework for Implementation Research (CFIR) [18]. Trained local interviewers fluent in relevant languages will conduct semi-structured interviews in private locations after obtaining verbal informed consent. Interview recordings and notes will be used for rapid qualitative analysis to immediately summarize each interview according to pre-defined domains, which will then be distilled into a matrix organized by domain and interviewee for analysis [22]. The first 5 interviews will be summarized by the group of interviewers as part of training to achieve consensus on the approach.Process mapping. Process mapping will be used to identify the flow of inputs required to achieve high MDA coverage, along with information on which aspects of the intervention are adaptable, and which are key determinants of high coverage. Following methods used in other MDA settings [23], we will use routine workflow tracking in the same CSIs selected for coverage evaluation surveys to record data on key activities during each round of MDA, including drug supply chain, training, sensitization, and the MDA itself. After 2 years, we will use coincidence analysis to identify any necessary and/or sufficient combinations of intervention activities that resulted in high MDA coverage [24].Costs and cost-effectiveness. Routine expenses will be tracked in all CSIs to monitor overall program costs, costs of program components (training, sensitization, delivery, administrative), costs per district, and costs per dose delivered. Incremental cost-effectiveness of the intervention compared to standard of care will be estimated using program costs, with effectiveness outcomes including measured mortality and estimated DALYs to calculate cost per death averted and cost per DALY averted.Fidelity. We will monitor CHW adherence to the intervention protocol using two methods: local CSI leaders will supervise CHWs in nearby communities according to their standard practice, and the study team will monitor fidelity to the protocol using standardized checklists in the same random sample selected for coverage evaluation surveys. These checks ensure the proper execution of program procedures, including eligibility assessment, dosing, adverse event monitoring, and data collection.

**Table 3 Tab3:** RE-AIM framework applied to AVENIR II outcomes

RE-AIM domain	Outcome definition	Data source
**Reach**	• Census coverage: proportion of eligible children treated, with numerator from CHW report and denominator from pregnancy history	• CHW data collection • Pregnancy history data collection
	• Administrative coverage: proportion of eligible children treated, with numerator from CHW report and denominator from MOH administrative data	• CHW data collection • MOH population estimates
	• Caregiver-reported coverage: proportion of eligible children treated according to caregiver report collected during coverage evaluation surveys	• Coverage evaluation survey
	• Coverage equity: coverage using above definitions in subgroups including child age, sex, caregiver age, caregiver education, household distance to CSI, community population density	• Coverage evaluation survey
**Effectiveness and cost-effectiveness**	**Effectiveness** • Under-5 mortality rate in treated vs delayed CSIs • Under-5 mortality rate in continue vs stop CSIs	• Pregnancy history data collection
	**Cost-effectiveness** • Incremental cost of azithromycin MDA compared to standard of care per death averted • Incremental cost of azithromycin MDA compared to standard of care per DALY averted	• Pregnancy history data collection • Cost data collection • DALY estimation
**Adoption**	• Proportion of eligible communities that receive MDA • Proportion of eligible CSIs that implement sensitization, training, and MDA delivery as intended	• Process mapping data collection
**Implementation**	**Costs** • Program costs, including training, sensitization, delivery, and administrative costs • Monitoring costs, including monitoring mortality, AMR, implementation, and safety outcomes	• Routine program and monitoring costs tracked in all CSIs
	**Fidelity** • Proportion of CHWs who deliver the intervention according to the protocol, overall and by component (eligibility assessment, dosing, adverse event monitoring, data collection)	• Supervision checklist data collection
	**Implementation strategies—**implementation strategies used during program delivery will be assessed during surveys and interviews • Acceptability of strategies measured on survey using locally adapted version of AIM instrument [16] and on interviews guided by CFIR outcomes addendum [17] • Appropriateness of strategies measured on survey using locally adapted version of IAM instrument [16] and on interviews guided by CFIR outcomes addendum [17] • Feasibility of strategies measured on survey using locally adapted version of FIM instrument [16] and on interviews guided by CFIR outcomes addendum [17]	• Coverage evaluation surveys • Interviews with caregivers, CHWs, and CSI leaders
**Maintenance**	• Coverage using above definitions over time • Costs of the program implementation and monitoring over time • Implementation strategies and contextual factors that impact maintenance assessed during interviews developed using CFIR [18]	• CHW data collection • Pregnancy history data collection • MOH population estimates • Coverage evaluation survey • Routine program and monitoring costs tracked in all CSIs • Interviews with caregivers, CHWs, and CSI leaders

#### Morbidity

Clinic visits will be monitored through passive surveillance at all CSIs. CSIs routinely record details of all clinic visits in logbooks which are aggregated into counts of specific diagnoses and treatments by CSI and entered into Niger’s DHIS2 database. All infectious-cause visits and cause-specific visits for diagnoses of respiratory infection, diarrhea, and malaria will be extracted among children under 5. Records will be regularly reviewed for eligible entries, and data including child age, community of residence, date of visit, diagnosis at visit, and treatment given will be extracted for all CSIs. Diagnoses of respiratory infection, diarrheal disease, and malaria at the CSIs are determined using the Integrated Management of Childhood Illness flowchart [15].

### Data collection, management, and monitoring

All study personnel who assess outcomes will attend 2-day training sessions prior to conducting study procedures. Training will include the operation of the mobile device where relevant, data collection through the mobile application or on paper, and the study protocol and procedures. Where possible, data will be collected electronically using custom-designed mobile applications (CommCare, Dimagi) on mobile devices and uploaded regularly to a secure, cloud-based server. Where possible, data will be uploaded in real-time using the cellular network, or weekly or monthly at a central site with strong Wi-Fi or cellular connection. Mobile devices will be encrypted and accessed via unique usernames and passwords. Mobile devices will be stored in locked offices with electricity for charging. Data on intervention administration will be recorded by community health workers on paper forms and later entered electronically.

Validation will be used in the development of the data collection forms to reduce inconsistencies and invalid entries. Data management teams in Niger and at UCSF will monitor data collection in real-time daily. Progress and quality control reports will be prepared and distributed to investigators weekly. Study participants will be assigned unique identification numbers that do not contain identifying information, which will be used to link data across databases and will be the only identifier shared in de-identified datasets.

### Study oversight

#### Niger MOH committee

Prior to the start of study activities, an MOH-based committee was established to approve the initial study design and protocols, approve protocol modifications, and oversee implementation of all activities. The committee includes MOH members with expertise in pediatrics, antimicrobial resistance, and community health interventions. Annual meetings will be held to review progress reports and make decisions about study continuation, recommendations from the DSMC, adding/dropping arms, and program implementation.

#### Institutional Review Boards

The Comité National Éthique pour la Recherche en Santé in Niger (14/2024/CNERS) and the University of California San Francisco Institutional Review Board (23-39839) have given ethical approval for the trial and will review the trial protocol annually.

#### DSMC

A DSMC was empaneled before the study began to provide independent oversight of data quality and participant safety. The DSMC includes independent experts with collective expertise in bioethics, biostatistics, antimicrobial resistance, and pediatric infectious disease. The DSMC will meet at least once per year to review study progress and adverse events, with ad hoc meetings convened as necessary. The DSMC will recommend modifications to the protocol as necessary.

In addition to the groups mentioned above, study investigators from UCSF and in Niger will monitor study conduct regularly through data monitoring as described previously in addition to regular site visits to ensure adherence to the study protocol. Two medical monitors with expertise in pediatrics and infectious disease will review the protocol before the trial begins and will review serious adverse events during the trial. The UCSF and Niger investigators will determine eligibility for authorship based on contributions to each manuscript and the related activities. Protocol modifications will be communicated to all relevant parties described here as well as community and CSI leaders as required by the Niger MOH committee.

### Sample size and power

For the overall program, we estimate that approximately 3 million children will be eligible to receive the intervention in approximately 1300 CSIs in 7 regions in Niger. We currently plan to monitor the primary mortality and AMR outcomes in 200 CSIs, evenly stratified across the 4 regions starting the program (Dosso, Tahoua, Maradi, Zinder). Calculations are presented for the first trial comparing treated to delayed arms and are assumed to apply to the second trial comparing continue to stop treatment arms as well.

#### Under-5 mortality rate (U5MR)

We estimate that monitoring a total sample of 200 CSIs, evenly split between MDA and delayed, would have 80% power to detect a reduction in the U5MR of 6.6 per 1000 live births. At 90% power, the reduction in U5MR is approximately 7.7 per 1000 live births. These estimates are based on a sample size equation for a t-test of cluster-level means. We assumed an alpha of 0.05 and a standard deviation of 16.6 in the CSI-level U5MR, which was estimated from the MORDOR Niger trial 5-year birth history substudy, which provided the most recent U5MR estimates available [25].

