#### Analysis

The primary analysis for U5MR will be to compare the proportion of children who die before age 60 months between the two arms. The prior likelihood for mortality will be estimated using cluster-level data from the AVENIR I trial, using methods similar to the likelihood estimation [3]. We will model CSI-level U5MR using a generalized linear regression model with terms for treatment arm and baseline U5MR. CSIs should be of similar size, but if we find there are large differences in size, then we will consider weighting the regression by the number of measurements in each CSI. We will estimate the likelihood of the data from the fitted regression model. Note that the MOH committee and DSMC will review and approve the prior used past the second year of the trial, with options including incorporation of new results outside of AVENIR I and II, as well as down-weighting the prior from AVENIR I over time.

To estimate the posterior, beginning with the maximum likelihood estimate of all parameters obtained by the generalized linear model, we will choose particular values of the treatment effect b. For each such value, we maximize the likelihood with respect to the other parameters, yielding the profile likelihood function with respect to the single parameter b. We will multiply the profile likelihood by the prior to obtain the posterior distribution, normalized to ensure the posterior likelihood sums to 1. We will derive Bayesian credible intervals from the posterior derived in this way. Specifically, we will report the 95% central coverage interval and the estimated median. We will also estimate the probability of the null hypothesis under the posterior likelihood, and its complement (the probability MDA reduces the U5MR). Subgroup analyses for U5MR include region, child age, child sex, and community distance to the CSI. Note that for analyses of the second trial comparing the continue vs stop arms, the first 6 months will be excluded from analyses to allow for a washout period to account for lingering effects from prior treatment.

The Bayesian credible intervals of the U5MR will also be used to compare the measured mortality rate against the Sustainable Development Goal (SDG) targets (a secondary outcome). We will estimate the probability that the U5MR is at or below the SDG target using the area of the posterior distribution that falls at or below the SDG target.

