Here we present a flexible design that allows for the evaluation not only of the azithromycin MDA intervention but others as well. As the epidemiologic landscape shifts over time, the effectiveness of child survival programs and priorities for community health may change. Azithromycin MDA for child survival may no longer be warranted as mortality declines or if the intervention contributes to detrimental increases in AMR. However, attributing effects to the program is challenging without a rigorous monitoring design. For example, longitudinal monitoring of AMR could show consistent increases over time due to antibiotic use outside of the program, even if azithromycin MDA remains effective in reducing mortality with only small and transient impacts on macrolide resistance. Thus, a monitoring design that allows for causal attribution is warranted. Moreover, despite the increasing popularity of and recent methodological advancements in adaptive and platform trials, the use of such methods in global health settings remains rare [32]. Among other benefits, adaptive designs can allow for more ethical randomization through methods like response adaptive randomization, enabling preferential treatment with more effective interventions over time [33]. Platform trials leverage the upfront investments made in trial infrastructure by examining multiple arms, dropping ineffective arms, and adding arms to adapt to new data and shifting priorities [6]. The use of an adaptive platform design allows us to monitor the impact of azithromycin MDA on mortality and AMR over time, enabling both the ability to determine whether to stop or continue the program as well as to evaluate other interventions as priorities shift.

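### The stated alpha and power for under-5 mortality describe a t-test without a prior, not the planned posterior analysis, whose AVENIR I prior favours MDA

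*Protocol article*

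**What the plan says.** The study design overview frames AVENIR II as two superiority trials. The sample size section on U5MR states that 200 CSIs in two equal arms "would have 80% power to detect a reduction in the U5MR of 6.6 per 1000 live births", and gives about 7.7 per 1,000 at 90% power. The basis is: "These estimates are based on a sample size equation for a t-test of cluster-level means". The inputs are: "We assumed an alpha of 0.05 and a standard deviation of 16.6 in the CSI-level U5MR". The opening of the sample size section carries the same calculation over to Trial 2.

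The Analysis section describes a different procedure. CSI-level U5MR is modelled on arm and baseline U5MR, the profile likelihood for the treatment effect is taken, and it is multiplied by a prior estimated from AVENIR I cluster-level data. The reported results are the posterior median, a 95% central interval and posterior probabilities: "We will also estimate the probability of the null hypothesis under the posterior likelihood, and its complement (the probability MDA reduces the U5MR"). No threshold for declaring benefit is given, and no discount of the prior is stated for Trial 1. For later use, the Ministry of Health committee and the DSMC "will review and approve the prior used past the second year of the trial", with down-weighting as one option.

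The Background reports that AVENIR I confirmed a mortality reduction and puts the effect in the West African trials at 14% to 18%. The Discussion allows that the effect may fade: "Azithromycin MDA for child survival may no longer be warranted as mortality declines".

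**The concern.** The sample size section and the Analysis section describe two different analyses, and error rates do not transfer from one to the other. A t-test without a prior holds its alpha when there is no effect. A posterior that starts from a favourable prior does not, if its interval is then read as a test.

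This matters because of what the trial is for. The Background aims to follow real-world effectiveness as conditions change, and the Discussion accepts that MDA may stop being warranted and that programme coverage may be lower and more variable than in the earlier trials. A prior that already points to benefit works against seeing a loss of effect. The article does not say that the result without the prior will be reported, so a high posterior probability of benefit could reflect AVENIR I as much as AVENIR II. Trial 1 is meant to guide programme expansion.

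**Working it through.** **1. The plan's own figures.** Inputs from the U5MR sample size section: SD 16.6 per 1,000, 100 CSIs per arm, alpha 0.05.

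- Standard error of the difference: s = 16.6 × √(2/100) = 2.348 per 1,000.
- Detectable difference, two-sided 0.05, normal formula: 2.348 × (1.960 + 0.842) = 6.58 at 80% power; 2.348 × (1.960 + 1.282) = 7.61 at 90%.
- Noncentral t with 198 degrees of freedom: 6.61 and 7.65.
- One-sided 0.05 would give 5.84 and 6.87, which does not match.

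The stated 6.6 and 7.7 are correct for a two-sided t-test. The nominal rate in the direction of benefit is therefore 2.5%.

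**2. The posterior analysis.** Write the prior mean as m, its SD as t, z = m/t, and r = s/t. With normal prior and likelihood, and benefit claimed when the 95% central interval excludes no effect:

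- False-benefit rate at zero true effect = Φ(z·r − 1.96·√(1 + r²)).
- Posterior probability of benefit when the AVENIR II estimate is exactly zero = Φ(z·r / √(1 + r²)).

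Assumptions not in the article: this success rule; an undiscounted prior centred on a 14% reduction (the low end of the Background's range), carried straight over to U5MR; a control U5MR of 100 per 1,000; the values of z; and no gain from baseline adjustment.

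On the log scale, m = |ln 0.86| = 0.1508 and s = 2.348/100 = 0.02348.

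| Prior z | r | Prior weight r²/(1+r²) | False-benefit rate | P(benefit) from exactly null data |
|---|---|---|---|---|
| 1.96 | 0.305 | 8.5% | Φ(0.598 − 2.049) = 7.3% | 72% |
| 2.5 | 0.389 | 13.2% | Φ(0.973 − 2.103) = 12.9% | 82% |
| 3 | 0.467 | 17.9% | Φ(1.401 − 2.163) = 22.3% | 90% |
| 3.5 | 0.545 | 22.9% | Φ(1.907 − 2.232) = 37.3% | 95% |

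On the absolute scale (m = 14, s = 2.348) the false-benefit rates at z 1.96, 2.5 and 3 are 7.8%, 14.1% and 24.7%. A simulation of the last case gave 24.5%.

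**3. How far the answer moves.**

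- Control U5MR 60 to 150, reduction 14% to 18%, z 1.96 to 4, undiscounted: 4.9% to 94%.
- Same grid with the prior at half weight: 3.5% to 40%. At 10% weight: 2.7% to 5.1%.
- Baseline adjustment with an assumed correlation of 0.5 shrinks s by √(1 − 0.25). For a 14% prior and U5MR 60 to 150 the rate is 5.2% to 10.8% at z 1.96 and 12% to 40% at z 3.
- Power at 6.6 per 1,000 with the undiscounted prior, U5MR 100 and 14%: 92% at z 1.96 and 98% at z 3, rather than 80%. Over the full grid it is 88% to nearly 100%.

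**The case against.** The strongest reply is that the article promises no error rate for its posterior. Alpha 0.05 enters for mortality only as an input to sizing, there is no posterior threshold, and a false-benefit rate needs a decision rule that the reader must supply. Sizing a Bayesian trial with a frequentist formula is not an error in itself, and here it is conservative for power. The borrowing is disclosed and deliberate, and any favourable informative prior raises the frequentist false-positive rate. Prior weights, thresholds and simulated operating characteristics commonly sit in an SAP, which is not shown. All of this stands, and it is why no single false-benefit rate can be pinned on the plan.

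It does not remove the point. The mismatch lies between two things the article states, not in something it omits. The probability of benefit given null data needs no threshold, because the plan commits to reporting that probability.

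A reader might infer that the false-benefit rate is well above the stated level. The documents do not support that as fact: prior precision, control U5MR, the gain from baseline adjustment and the mapping from the 1–59-month mortality used in AVENIR I to U5MR are all unstated, and the mild end of the range (4.9%) is not above 0.05 itself.

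A reader might also infer that Trial 2 must use a flat prior as primary because AVENIR I compared treatment with placebo, not continuing with stopping. That is a design preference. The article does not fix the AVENIR I prior for Trial 2; it sends the prior to review. Nor is it a fault that the reviewing committees may know Trial 1 results. Those are not Trial 2 outcomes, and nothing says the prior would be chosen after year-4 data are seen.

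**Conclusion.** The point holds in a limited form. The 6.6 and 7.7 per 1,000 are right for the test they name, but that test is not the primary analysis, so the alpha and power do not describe it. If benefit is read from the 95% interval under an undiscounted prior that itself excludes no effect, the false-benefit rate exceeds 2.5% in every case computed. The amount is conditional: about 7% to 8% at prior z 1.96 and 22% to 25% at z 3, for a 14% prior and U5MR of 100 per 1,000, and close to nominal if the prior is heavily discounted. That z is at least 1.96 is inferred only from the Background's statement that AVENIR I confirmed the reduction.

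The more practical consequence is the reported probability of benefit. Under the same assumptions, it would be about 72% (z 1.96) to 95% (z 3.5) when AVENIR II itself shows nothing. For a trial meant to notice whether the programme still works, this should be corrected, although it does not invalidate the design.

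**What to change.** 1. In the U5MR sample size section, label the alpha and power as applying to the analysis without the prior. Alternatively, replace them with simulated type I error and power for the planned posterior analysis, stating the prior weight and the decision rule used.
2. For each trial, report the AVENIR II-only result (same model, flat prior) beside the borrowed posterior, and base statements on current programme effectiveness on it. The profile likelihood is computed before the prior is applied, so this result is already available.
3. For Trial 2, fix and date the approved prior before any year-4 outcome is unmasked.

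The cost is a labelling change or a small simulation, one more reported line per trial, and a dated record of the prior. The downside is a wider interval for the AVENIR II-only result. No new data or design change is needed.
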